## Abstract

**Background:**

AmBisome^® ^is an efficacious, safe anti-leishmanial treatment. There is growing interest in its use, either as a single dose or in combination treatments. In East Africa, the minimum optimal single-dosage has not been identified.

**Methods/Design:**

An open-label, 2-arm, non-inferiority, multi-centre randomised controlled trial is being conducted to determine the optimal single-dose treatment with AmBisome^®^.

Patients in the single-dose arm will receive one infusion on day 1, at a dose depending on body weight. For the first group of patients entered to the trial, the dose will be 7.5 mg/kg, but if this dose is found to be ineffective then in subsequent patient series the dose will be escalated progressively to 10, 12.5 and 15 mg/kg. Patients in the reference arm will receive a multi-dose regimen of AmBisome^® ^(3 mg/kg/day on days 1-5, 14 and 21: total dose 21 mg/kg). Patients will be hospitalised for approximately one month after the start of treatment and then followed up at three and six months. The primary endpoint is the status of patients six months after treatment. A secondary endpoint is assessment at day 30. Treatment success is determined as the absence of parasites on microscopy samples taken from bone marrow, lymph node or splenic aspirates. Interim analyses to assess the comparative efficacy of the single dose are planned after recruitment of 20 and 40 patients per arm. The final non-inferiority analysis will include 120 patients per arm, to determine if the single-dose efficacy 6 months after treatment is not more than 10% inferior to the multi-dose.

**Discussion:**

An effective, safe single-dose treatment would reduce hospitalization and treatment costs. Results will inform the design of combination treatment studies.

**Trial Registration:**

ClinicalTrials.gov NCT00832208

## Background

Visceral Leishmaniasis (VL) is a parasitic disease that is transmitted by phlebotomine sandflies, and is fatal if not treated. Estimates suggest there are 500,000 cases per year, with 90% of cases occurring in India, Bangladesh, Nepal, Sudan, Kenya, Ethiopia and Brazil [1,2]. In East Africa, the disease has been known to occur in cyclical epidemics, one of which resulted in over 100,000 deaths in Southern Sudan between 1984-94 [3,4]. Parasitological diagnosis is determined by lymph node, bone marrow and spleen aspirates. The mainstay of control in East Africa, where the disease is believed to be largely anthroponotic, has been case finding and treatment. Treatment options for VL in the region has been limited to antimonials (sodium stibogluconate or glucantime), given intramuscularly (IM) or intravenously (IV) for 28-30 days. This long and relatively toxic treatment is inconvenient for patient management. Two other treatments; paromomycin, a 3- week IM treatment, and miltefosine, a 4-week oral treatment, have recently been developed and registered for VL in India. Both are in development in Africa, but both require relatively long courses, have some toxicity and there are contraindications and issues with compliance [2].

AmBisome^®^, a liposomal formulation of Amphotericin B has been shown to be safe and effective against leishmaniasis. In trials in India, an efficacy of 90% was obtained with a single dose of 5 mg/kg [5,6]. A major limitation of this treatment has been its cost but recently, the drug has been offered at a preferential price for the treatment of VL by its producer, Gilead. This has raised considerable interest in its use either as a single dose treatment or as part of a combination treatment where a single dose of AmBisome^® ^might be followed by a short course of a companion drug such as miltefosine[7]. There are limited data on the use of AmBisome^® ^in East Africa. One small phase II trial in Kenya showed an efficacy of 20% at a total dose of 6 mg/kg, 90% at a total dose of 10 mg/kg and 100% at a total dose of 14 mg/kg [8].

At the time of developing this study protocol, there was a recommendation made to use AmBisome^® ^in East Africa at a total dose of 21 mg/kg [9] but this recommendation was based on experience with the drug in India and it is not known if this is the appropriate dose for use in the treatment of African patients. That there might be geographical difference in drug efficacy is illustrated by a recent study conducted by the authors, as members of the Leishmaniasis East Africa Platform (LEAP), and Drugs for Neglected Diseases initiative (DNDi), which showed that the efficacy of paromomycin for VL, is lower in East Africa, than in India[10]. There is a clear need 1) to demonstrate the efficacy of AmBisome^® ^given under the standard recommended multiple dose regimen; and 2) to determine if lower single doses of AmBisome^® ^could be used to treat VL.

## Methods/Design

### Study Design

An open-label, non-inferiority, multi-centre, individually randomised controlled trial.

### Main Hypothesis

The hypothesis is that a sufficiently large single dose of AmBisome^® ^is safe and is not inferior in efficacy to a multiple dose regimen of AmBisome^®^.

### Main Objective

To determine the minimum single-dose treatment regimen of AmBisome^® ^that is efficacious and safe.

### Setting

Trial sites are in three locations, each in endemic areas for VL. These are Gondar University Hospital in Amhara State - Ethiopia; Arba Minch Hospital, Southern Nations, Nationalities and Peoples State - Ethiopia; and Kassab Hospital, Gedarif State, Sudan. All data collected in the trial are analysed in the data centre located at the Coordination Centre for the trial at the Kenya Medical Research Institute (KEMRI) in Nairobi, Kenya.

### Outcome measures

#### Primary outcome

*Definitive Cure *- defined as absence of parasites 6 months after the end of the 30 hospitalisation period following the initiation of treatment (i.e., 7 months after the start of treatment), confirmed by splenic or bone marrow aspiration.

#### Secondary outcomes

*Initial Cure* - defined as parasitological clearance, measured on day 30 after initiation of treatment on day 1, confirmed by lymph node, splenic or bone marrow aspiration.

### Sample Size

The final analysis will be based on the primary efficacy endpoint of definitive cure. Assuming a true efficacy of 95% in both arms, 120 patients per arm will provide 80% power to detect if the efficacy of the single-dose treatment regimen is no more than 10% inferior to the reference multi-dose regimen[11].

The trial design allows for a dose escalation in the single-dose arm at the pre- specified interim analysis time points if the single-dose regimen is found to be performing poorly, compared to the multi-dose and based on a test of difference in the proportion of patients achieving initial cure, measured at the secondary efficacy endpoint on day 30 (Figure 1). Based on a two-sided significance test for a difference in proportions at the 5% level assuming 95% efficacy in the reference arm, 20 patients per arm will provide approximately 80% power to detect a difference if the test arm is less than 60% effective and 40 patients per arm will provide 80% power to detect a difference in efficacy if the test arm is less than 70% effective [12].

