### Type of analysis

The final analysis will be based on a comparison of definitive cure of the single-dose treatment regimen to the reference treatment regimen. If the treatments in the two arms are equally efficacious, the trial is powered such that the confidence interval around the difference in efficacies of the two regimens will be no more than 10% (non inferiority margin Δ = 0.1). The primary analysis will be by intention to treat (ITT). A per-protocol (PP) analysis will exclude patients deemed to have major protocol deviations but include minor deviations, where major and minor deviations are pre-specified prior to recruitment.

Two interim analyses are planned after recruitment of a pre-specified number of patients per arm, to allow for rapid elimination of inadequate dosage regimens. The interim analysis will be assessed at the secondary endpoint, initial cure, measured on day 30, where treatment is initiated on day 1 (Figure 1).

The first single-dose regimen tested will be 7.5 mg/kg body weight. Interim analyses are planned after recruitment of 20 and 40 patients per arm. Randomisation will pause once the desired number of patients for each interim analysis has been recruited, in order to carry out the interim analysis and assess if the trial will continue with the current single-dose or a higher single-dose. If interim results indicate a Fisher's test of a difference with a p-value ≤ 0.05, randomisation will re-start with the next highest dose in the single-dose regimen arm. Interim analyses will take place as pre-specified for each dosage tested in the single-dose treatment arm.

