### Dissemination of Results

An interim analysis report presenting the efficacy (95% confidence intervals) in each arm and the p-value from a Fisher's test of a difference will be provided to the DSMB. This report will also contain a listing of serious adverse events. The DSMB will review the results and report back to the coordination group, to confirm if the stopping rule for a single-dose has been met. Adverse event listings are to be provided at the request of the DSMB. The DSMB, through the Chair may request additional efficacy and safety data if they have concerns relating to trial conduct or other ethical and safety issues [19]. At the end of the trial, the analysis report will be circulated to Principal Investigators, DSMB, Ethics Committees, Ministries of Health and Drug Regulatory Authorities.

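### Under the protocol's own Fisher rule, the first interim has about 72% power at 95% versus 60%, not approximately 80%

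*Protocol article*

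**What the plan says.** The Sample Size section of the protocol article gives the power of both interim comparisons. The basis is set out as "Based on a two-sided significance test for a difference in proportions at the 5% level", "assuming 95% efficacy in the reference arm". It then says that "20 patients per arm will provide approximately 80% power to detect a difference if the test arm is less than 60% effective" and that "40 patients per arm will provide 80% power to detect a difference in efficacy if the test arm is less than 70% effective". The section does not name the test used for these figures.

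The deciding test is named elsewhere. Under Type of analysis, escalation is triggered as follows: "If interim results indicate a Fisher's test of a difference with a p-value ≤ 0.05". Dissemination of Results confirms it: "the p-value from a Fisher's test of a difference will be provided to the DSMB". The endpoint is binary ("The interim analysis will be assessed at the secondary endpoint, initial cure, measured on day 30"), and the looks are equally sized by arm ("Interim analyses are planned after recruitment of 20 and 40 patients per arm").

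**The concern.** The power is stated for an unnamed test of two proportions, while the decision uses Fisher's test. Fisher's test is conservative when groups are small and one proportion is close to 1, which is the situation here: 20 per arm and a reference rate of 95%. A power figure from an uncorrected large-sample formula will then overstate what the rule delivers.

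The interim looks are meant to remove poor single doses early, and the same scheme is repeated for each dose tested. If the first look is less sensitive than stated, more patients are randomised to an inadequate dose before the second look, and the DSMB and ethics committees have been given too favourable a figure for it.

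**Working it through.** **Inputs.** Reference rate 0.95, test-arm rate 0.60 (the boundary named in the text), n = 20 per arm, two-sided 5% (all from Sample Size). Fisher's test, reject if p ≤ 0.05 (Type of analysis). For the second look: n = 40 per arm, 0.95 versus 0.70.

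**Step 1: where the stated figure may come from.** With d = 0.95 − 0.60 = 0.35 and mean rate 0.775:

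- Standard error under no difference: √(2 × 0.775 × 0.225 / 20) = 0.1320.
- Standard error under the alternative: √((0.95 × 0.05 + 0.60 × 0.40) / 20) = 0.1199.
- Pooled z-test: Φ[(0.35 − 1.96 × 0.1320) / 0.1199] = Φ(0.76) = 77.7%.
- Unpooled z-test: Φ(0.35 / 0.1199 − 1.96) = Φ(0.96) = 83.1%.
- Arcsine approximation: 82.8%. Exact power of the uncorrected chi-square test: 82.0%.

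The uncorrected methods run from 77.7% to 83.1%, around the stated figure. The pooled formula needs 22 per arm for 80%.

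**Step 2: power of the rule as written.** Power = Σ P(A = a) P(B = b) over all tables with two-sided Fisher p ≤ 0.05, where A ~ Binomial(20, 0.95) and B ~ Binomial(20, 0.60).

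| Reference cures | P(A = a) | Single-dose cures needed to reject | P(B at or below this) | Product |
|---|---|---|---|---|
| 20 | 0.3585 | ≤ 15 (p = 0.047; 16 gives 0.106) | 0.9490 | 0.3402 |
| 19 | 0.3774 | ≤ 13 (p = 0.044; 14 gives 0.092) | 0.7500 | 0.2830 |
| 18 | 0.1887 | ≤ 11 (p = 0.031; 12 gives 0.065) | 0.4044 | 0.0763 |
| 17 | 0.0596 | ≤ 10 | 0.2447 | 0.0146 |
| 16 | 0.0133 | ≤ 9 | 0.1275 | 0.0017 |

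These rows sum to 0.7158. The remaining tables bring the total to 0.7159, so power is **71.6%** and the miss rate is 28.4%.

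**Step 3: where 80% is reached.** At 20 per arm, two-sided Fisher power by single-dose rate is 59%: 73.9%; 58%: 76.0%; 57%: 78.1%; 56%: 80.0%; 55%: 81.8%. At 60%, 23 per arm gives 79.8% and 24 gives 82.1%.

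**Step 4: the second-look statement.** The same enumeration at 40 per arm, 95% versus 70%, gives 82.1%. That statement holds at its own boundary.

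**Step 5: both looks together.** Take the second look as cumulative (the first 20 per arm plus 20 more). For a 60%-effective dose, exact joint enumeration gives 71.6% dropped at the first look and a further 25.9% at the second, so 97.5% in all. Relative to the stated 20% miss rate, the extra exposure averages (0.284 − 0.20) × 20 ≈ 1.7 single-dose patients per such dose.

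**The case against.** The text says approximately 80% and below 60%, and rates of 56% or lower do fall in that range with at least 80% power. The figure also agrees with ordinary large-sample methods, so it is better described as a mismatch between the power formula and the deciding test than as an arithmetic slip. Both remarks are fair, and they limit the weight of the point. They do not remove it. The sentence presents 60% as the boundary for about 80% power, the parallel sentence for 40 per arm is true at its boundary, and a gap of about 8 percentage points is more than rounding.

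Three stronger readings are tempting, and the document does not support them.

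- *That a significant result in favour of the single dose would trigger escalation.* The trigger sentence under Type of analysis gives no direction when read alone. But Sample Size ties escalation to a single dose doing poorly against the multi-dose regimen, the section on single-dose regimens requires that the dose be ineffective, and the DSMB confirms whether the rule is met. The event is also very rare: about 0.09% at 20 per arm when both arms are at 95%.
- *That poor doses would be carried forward to the final analysis.* The second look catches most of those missed, as Step 5 shows.
- *That a one-sided 5% Fisher test would repair the figure at almost no cost.* It does give 80.8% at 20 per arm. At 95% in both arms the chance of abandoning the dose over both looks rises only from 0.5% to 0.8%. For a 90%-effective dose, however, it rises from 5.1% to 9.4%, and for an 85%-effective dose from 20.3% to 30.0%. The trial's aim is to find the smallest single dose that works, so this is a real trade-off and a change of design.

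**Conclusion.** The first-interim power statement is wrong for the test that the protocol specifies: 71.6% at 95% versus 60%, against a stated figure of approximately 80%. The consequence is mainly a delayed decision on a dose near 60%. The primary endpoint, the 120 patients per arm, the margin and the final non-inferiority analysis are untouched. Severity: minor.

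The result assumes that the Fisher test is two-sided (Sample Size says so for the interim comparison; the trigger sentence does not repeat it), that day-30 cure in the reference arm is 95%, and that all 20 patients per arm are evaluable. The 97.5% figure further assumes a cumulative second look at the same dose. That the stated 80% came from an uncorrected large-sample formula is an inference, since the document does not name the method.

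**What to change.** Keep the two-sided Fisher rule at p ≤ 0.05 and correct the sentence in Sample Size. It should say that, with Fisher's two-sided test and 95% in the reference arm, 20 patients per arm give about 72% power if the single dose is 60% effective, and 80% if it is about 56% effective. Name Fisher's test there, so that the power statement and the decision rule refer to the same test. The 40-per-arm statement can stand.

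The cost is one sentence of text, with no extra patients and no change to the decision rule or any analysis.

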**Figure 1 F1:**
[figure not shown]
**Trial Flow CONSORT Diagram**. ^1 ^dosage: 3 mg/kg on days 1-5, 7 and 14 (total dose 21 mg/kg). ^2 ^possible single-doses of 7.5, 10, 12.5 & 15 mg/kg on day 1.

### Choice of NI margin

A margin of 10% below an assumed efficacy of 95% was considered acceptable based on clinical acceptability given the limited availability of possible treatments for VL and sample size considerations based not only on power but on recruitment time projections.

### Allocation

Patients will be randomised to one of two treatment arms; either the reference multi- dose regimen or the test single-dose regimen.

Block randomisation by site will be used to minimise imbalance in multi-centre interim analyses. The user-written program *ralloc *for Stata will be used to obtain the final sequence[13]. The process of randomisation generation and the resulting final randomisation list, produced by the trial statistician will be kept securely at the DNDi Data Centre. Sequentially numbered, sealed, opaque envelopes will conceal random allocation to treatment until immediately prior to receipt of first treatment administration.

Blinding of the patients or clinicians was not considered feasible or ethical; placebo injections in the single-dose arm would have caused additional unnecessary discomfort to patients.

### Interventions

#### Multiple-dose regimen

A total dose of 21 mg/kg given as a 3 mg/kg intra-vascular (IV) infusion on days 1,2,3,4,5,14 and 21, was chosen as the reference treatment regimen, expected to achieve efficacy of 95% [9,14].

#### Single-dose regimen(s)

The trial will compare only one single-dose test regimen to the multi-dose regimen during any one recruitment period but the trial design does allow for testing of incrementally higher single-doses in later recruitment periods if lower doses are ineffective (see above and Type of Analysis section).

Based on experience from treatment trials for VL in India and Kenya[15], either 7.5 mg/kg or 10 mg/kg is likely to be the lowest dose to show suitable efficacy in a single-dose regimen [14-16] although the efficacy of treatment regimens used in India can be substantially lower in African setting [8,10]. The trial will begin with a 7.5 mg/kg single-dose regimen in the test arm. If this regimen is found to be ineffective according to pre-specified criteria at the time of an interim analysis, the trial design allows for recruitment and randomisation into the two arms to continue with a higher single-dose (see Type of Analysis section). Higher single doses to be used, if 7.5 mg/kg is ineffective, are 10 mg/kg,12.5 mg/kg and 15 mg/kg. It is considered that 15 mg is the maximum dose that can be safely administered as a single-dose [15].

### Screening

#### Inclusion criteria

Aged 4 years or older; VL proven by parasitological examination of splenic aspirate, lymph node or bone marrow aspirate; haemoglobin >4 g/dL; fever for more than 2 weeks; written informed consent to participate (for children, by parent or guardian); HIV negative status.

#### Exclusion criteria

'In extremis' signs/symptoms of severe VL; receipt of anti-leishmanial treatment or investigational (unlicensed) drugs within previous 6 months; known underlying chronic disease, such as severe cardiac, pulmonary, renal, or hepatic impairment; renal function tests (serum creatinine) outside the normal range; liver function tests more than 3 times the normal range; platelet count less than 40,000/mm^3^; known alcohol abuse; pregnancy or lactation; concomitant acute drug usage for malaria and bacterial infection, pneumonia within previous 7 days; known hypersensitivity to AmBisome^® ^or amphotericin B.

In addition, patients presenting with severe dehydration should be re-hydrated before consideration for trial entry and those presenting with acute bacterial co-infection e.g. malaria, pneumonia must have these infections treated prior to trial entry. In the Sudanese site, recruitment until the end of the first interim analysis period will include those aged 12 years and above before widening to age 4 years and above, at the request of the Sudanese Ethics Committee.

### HIV-status and VCT

All patients (or parents/guardians) will be offered Voluntary Counselling & Testing (VCT) for HIV screening/testing in accordance with national guidelines. This trial specifically requires HIV negative patients, therefore patients who refuse counselling and testing, or who test positive will be excluded from the trial, but will be treated for VL according to national guidelines and if HIV positive referred to national HIV treatment programs for assessment and treatment with anti-retrovirals (ARVs) if indicated.

### Consent

Standardised consent forms, adapted to the local context, translated into local languages and approved by ethics committees are to be used. Signatures or thumbprints will be obtained for consent, with witnesses in the case of illiterate subjects. Parents or guardians will be asked to provide consent for all children and in Ethiopia, depending on their age and level of comprehension, children will be asked to give their assent, as required by local regulations.

Patients who do not meet inclusion criteria or who do not give consent will be treated outside the trial, according to national treatment guidelines.

### Type of analysis

The final analysis will be based on a comparison of definitive cure of the single-dose treatment regimen to the reference treatment regimen. If the treatments in the two arms are equally efficacious, the trial is powered such that the confidence interval around the difference in efficacies of the two regimens will be no more than 10% (non inferiority margin Δ = 0.1). The primary analysis will be by intention to treat (ITT). A per-protocol (PP) analysis will exclude patients deemed to have major protocol deviations but include minor deviations, where major and minor deviations are pre-specified prior to recruitment.

Two interim analyses are planned after recruitment of a pre-specified number of patients per arm, to allow for rapid elimination of inadequate dosage regimens. The interim analysis will be assessed at the secondary endpoint, initial cure, measured on day 30, where treatment is initiated on day 1 (Figure 1).

The first single-dose regimen tested will be 7.5 mg/kg body weight. Interim analyses are planned after recruitment of 20 and 40 patients per arm. Randomisation will pause once the desired number of patients for each interim analysis has been recruited, in order to carry out the interim analysis and assess if the trial will continue with the current single-dose or a higher single-dose. If interim results indicate a Fisher's test of a difference with a p-value ≤ 0.05, randomisation will re-start with the next highest dose in the single-dose regimen arm. Interim analyses will take place as pre-specified for each dosage tested in the single-dose treatment arm.

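### Non-inferiority is to be judged on ITT as the sole primary analysis, and the planned per-protocol analysis has no stated part in the conclusion, although only the reference regimen can be left incomplete after day 1

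*Protocol article*

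**What the plan says.** Under Type of analysis, the article states "The primary analysis will be by intention to treat (ITT". The next sentence adds "A per-protocol (PP) analysis will exclude patients deemed to have major protocol deviations but include minor deviations". The two categories are to be fixed in advance: "where major and minor deviations are pre-specified prior to recruitment". It does not say whether PP must agree with ITT, whether it is supportive only, or what follows if the two disagree. The margin is given as "non inferiority margin Δ = 0.1".

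The abstract (Methods/Design) puts the final decision on the planned full sample: "The final non-inferiority analysis will include 120 patients per arm, to determine if the single-dose efficacy 6 months after treatment is not more than 10" percentage points below the reference. Sample Size gives the planning basis: "Assuming a true efficacy of 95% in both arms, 120 patients per arm will provide 80% power". No allowance for exclusions from a PP set is stated.

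The regimens differ in what can go undelivered. The single-dose arm has one infusion on day 1. The Multiple-dose regimen section describes the reference as an "infusion on days 1,2,3,4,5,14 and 21". The abstract says that patients stay in hospital for about a month, so all of these infusions fall within the admission.

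Primary outcome defines definitive cure by absence of parasites six months after the hospital period. It does not say how a patient who has received rescue treatment is classified, although Rescue medication provides for such treatment in both arms.

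**The concern.** In a superiority trial, ITT usually errs towards no difference, which is the cautious direction. In a non-inferiority trial that same error favours the claim. Anything that lowers cure in the reference arm, or makes the arms alike, narrows the observed deficit of the test arm.

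Here the exposure is one-sided. Once day 1 has passed, the single-dose regimen has been fully given and only the reference regimen can be under-delivered. The article itself foresees one route, withdrawal from treatment for an adverse reaction, and early self-discharge is another. A PP analysis would show whether the ITT result depended on such patients. As written, however, a trial that met the margin on ITT and missed it on PP could still be declared non-inferior.

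The outcome definition adds a second route. Read literally, a single-dose patient who fails, receives rescue and is parasite-free at the last visit could count as a definitive cure. That too would make the arms alike under ITT.

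**Working it through.** **1. The protocol's own figure.** Inputs from Sample Size and Type of analysis: 95% cure in both arms, margin 0.10, 120 per arm, 80% power. The alpha of the final test is not stated. The 5% level in "Based on a two-sided significance test for a difference in proportions at the 5% level" belongs to the interim test. I assume one-sided 0.025, that is, a two-sided 95% interval.

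- The usual unpooled formula gives 75 per arm, and 94.5% power at 120. It does not reproduce the plan.
- Taking the variance at the margin (85% against 95%) for alpha, and at 95%/95% for power: n = [1.96 × √(0.85×0.15 + 0.95×0.05) + 0.842 × √(2×0.95×0.05)]² / 0.10² = 117 per arm, with 81.4% power at 120. This does reproduce it, under the assumed alpha.

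**2. Effect of incomplete reference treatment on ITT.** Let a fraction f of reference patients be incomplete and a fraction q of those be cured. Both are assumptions. Reference cure under ITT is 0.95(1 - f) + q·f. The single dose is set at 85%, exactly at the margin against a fully treated reference of 95%. The table gives the probability that the Newcombe 95% lower limit exceeds -10 points, by exact binomial enumeration at 120 per arm.

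| f | q | Reference cure under ITT | False non-inferiority |
|---|---|---|---|
| 0 | - | 95.0% | 2.4% |
| 5% | 90% | 94.75% | 2.7% |
| 10% | 90% | 94.5% | 3.2% |
| 15% | 90% | 94.25% | 3.6% |
| 5% | 50% | 92.75% | 7.5% |
| 10% | 50% | 90.5% | 17.7% |

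**3. Which q is plausible.** A patient who receives the infusions of days 1-5 and none after has had 5 × 3 = 15 mg/kg. The Background reports, from one small phase II trial, cure of 20% at a total of 6 mg/kg, 90% at 10 mg/kg and 100% at 14 mg/kg. Late omissions therefore correspond to q of about 90% or more, the upper rows. The lower rows need patients to stop within the first few infusions.

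**4. What PP would do.** Suppose incomplete reference patients are excluded and those who remain are cured at 95%. False non-inferiority is then 2.4% with 120 against 114 patients and 2.6% with 120 against 108. This assumes that the excluded patients do not differ in prognosis from the rest.

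**5. Power if both sets must pass.** True cure is 95% in both arms, with exclusions unrelated to outcome. Newcombe power for ITT at 120 per arm is 90%.

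| PP patients per arm | PP alone, Newcombe | ITT and PP jointly, Newcombe (simulated) | PP alone, step 1 formula |
|---|---|---|---|
| 108 | 87% | 86% | 76% |
| 100 | 83% | 82% | 72% |

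**The case against.** Four points can be made against this.

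**Adherence.** A reader might infer that reference patients must come back for infusions over three weeks, so that missed visits are to be expected. The documents do not support that. Patients are in hospital for about a month, and Table 1 lists days 1 to 30 as inpatient assessment. This makes a high rate of missed infusions less likely. It does not exclude withdrawal for an adverse reaction or early self-discharge.

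**Size.** A reader might also suppose that late omissions cut cure to 70-80%. With 15% incomplete and 70% cured, false non-inferiority would be 13.7%. The article's only dose-response figures point to 90% or more after 15 mg/kg, so that figure should not be used for late omissions. The objection stands for late omissions but not for early stopping. The dose-response source is also one small trial, and the Background says that the right dose for African patients is unknown.

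**Silence.** That PP has no role at all would be read from silence. PP is planned, deviations are fixed before recruitment, and the full protocol or SAP may say how the two analyses are weighed. ITT as primary with a PP analysis alongside is a recognised approach. This is fair, and the point is limited to what the article states: ITT is the sole primary analysis, and no part in the conclusion is stated for PP.

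**PP has its own bias.** It drops patients after randomisation, in an open-label trial, and is not automatically conservative. This stands, and it is why PP should be required alongside ITT and not in its place.

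**Conclusion.** The point holds in a limited form. The article makes ITT the sole primary analysis of a non-inferiority comparison and states no part for PP in the conclusion. Any under-treatment after day 1 can fall only on the reference arm, and under ITT it favours the single dose.

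The direction is certain and the size is not. If incomplete patients miss only late infusions, the inflation is small: from 2.4% to at most 3.6% with up to 15% incomplete. It becomes serious, 7.5-17.7%, only if 5-10% of reference patients stop early and half of them are cured. These figures rest on assumed rates, a single dose truly at 85%, a one-sided 2.5% level and the Newcombe interval. The documents do not show that an inferior dose would be passed, only that the stated rule does not guard against it.

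This is an inexpensive improvement to the decision rule and not the correction of an error in the arithmetic.

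**What to change.** In Type of analysis, state that non-inferiority is concluded only if the lower limit of the 95% confidence interval for the difference in definitive cure (single dose minus multi-dose) is above -10 points in both the ITT and the PP population. ITT stays primary and PP is an added condition.

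In the same place, state that patients with treatment failure or rescue count as failures in both sets, and are not removed from PP as deviators. The Primary outcome definition should say the same.

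The cost is two sentences, since the PP analysis and its deviation rules are already planned, plus some power. By the Newcombe interval, joint power falls from about 90% to 86% with 108 PP patients per arm and 82% with 100. Under the formula that reproduces 120 per arm, PP power is 76% at 108, and joint power cannot exceed that. The 80% in Sample Size should therefore be stated as applying to ITT. If 120 patients per arm were wanted in PP as well, 10% exclusions would mean randomising 120/0.90, or 134 per arm.
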